## Abstract

**Background:**

Rates of participation in Diabetes Prevention Programs (DPPs) are low. This may be due, in part, to low levels of autonomous motivation (i.e., motivation that arises from internal sources and sustains healthy behaviors over time) to prevent type 2 diabetes (T2DM) among many individuals with prediabetes. Mobile health (mHealth) technologies that incorporate principles from the Self-Determination Theory offer an effective and scalable approach to increase autonomous motivation levels. One promising mobile phone-based application is JOOL Health, which aims to help users connect certain health behaviors (e.g., sleep and diet) with personal values in specific life domains (e.g., family and work). The first aim of this study is to estimate whether JOOL Health can increase autonomous motivation to prevent T2DM among individuals with prediabetes who declined DPP participation. The second aim of this pilot study is to examine the intervention’s feasibility and acceptability.

**Methods:**

This is a 12-week, three-arm pilot randomized controlled trial. We will recruit 105 individuals with prediabetes who did not engage in a DPP despite invitation from their health plan to participate in face-to-face or web-based programs at no out-of-pocket-cost. Participants will be randomized to one of three study arms: (1) a group that receives information on prediabetes, evidence-based strategies to decrease progression to T2DM, and a list of resources for mHealth tools for monitoring diet, physical activity, and weight (comparison group); (2) a group that receives the JOOL Health application; and (3) a group that receives the JOOL Health application as well as a Fitbit activity tracker and wireless-enabled scale. Our primary outcome is change in autonomous motivation to prevent T2DM (measured using the Treatment Self-Regulation Questionnaire). We will also collect data related to the intervention’s feasibility (recruitment and retention rates) and acceptability (adherence and qualitative experience) as well as changes in psychosocial outcomes, hemoglobin A1c, and weight.

**Discussion:**

To our knowledge, this is the first study that aims to promote positive health behaviors among individuals with prediabetes who previously declined to participate in a DPP. Our results will inform a larger trial to test the effect of JOOL Health on clinically relevant outcomes, including weight loss, physical activity, and DPP engagement.

**Trial registration:**

NCT03025607. Registered February 2017.

**Electronic supplementary material:**

The online version of this article (10.1186/s40814-018-0246-z) contains supplementary material, which is available to authorized users.

## Background

Within the USA, type 2 diabetes mellitus (T2DM) and its precursor, prediabetes, are growing public health concerns. Approximately 84 million adults have prediabetes [1], and it is estimated that one-third of the adult population will have T2DM by 2050 [2]. Diabetes Prevention Programs (DPPs) can promote modest weight loss [3–8] to help individuals with prediabetes avoid progression to T2DM [9–11], and these programs are available in communities throughout the USA [4, 12].

Despite nationwide availability of the DPP [4] and public health initiatives to identify and treat individuals with prediabetes [13, 14], rates of DPP engagement are extremely low [15]. Barriers to DPP participation include logistical factors (e.g., transportation, time, cost) [16] and behavioral factors (e.g., motivation, risk perception) [17–19]. Although web-based DPPs [20, 21] and growing insurance coverage for program participation [22–24] can reduce logistical barriers, these strategies alone have been inadequate to increase rates of DPP engagement. In September 2015, for example, a single University’s self-funded health insurers began to offer face-to-face and online DPP options to healthcare plan members (i.e., employees, retirees, and students of the University or their dependents) with prediabetes at no out-of-pocket-cost, yet only 6% of invitees enrolled in a DPP within 6 months. Prior work demonstrates an association between greater levels of autonomous motivation and increased engagement in healthy behaviors among this university’s employees with prediabetes [25]. This finding, in combination with low levels of program engagement, suggests that behavioral barriers may more strongly influence rates of DPP participation than logistical ones.

New strategies are needed to motivate individuals with prediabetes to engage in healthy behaviors to prevent T2DM. Mobile health (mHealth) technologies that incorporate principles from behavioral change theories such as Self-Determination Theory (SDT) may be an effective and highly scalable approach [26]. SDT provides a conceptual framework for understanding human behavior across a continuum of motivation ranging from controlled motivation to autonomous motivation [27]. In contrast to controlled motivation, which originates from a sense of external obligation or pressure, goals and behaviors are “autonomous” when they align with personal interests and values [28]. Greater levels of autonomous motivation correlate positively with dietary adherence [29], weight loss [30, 31], physical activity [32, 33], and DPP participation [34]. Importantly, autonomous behaviors are sustained over time [35, 36].

JOOL Health is a mobile phone-based health application that aims to increase autonomous motivation by helping users connect certain health behaviors (e.g., sleep, diet, physical activity) with personal values in specific life domains (e.g., family and work) [37]. JOOL Health integrates user-entered information with contextual data (e.g., weather and day of the week) and then delivers tailored messages to help individuals gain awareness of and control over the factors that contribute to their well-being and ability to engage in self-care behaviors. In this way, JOOL Health aims to cultivate autonomous sources of motivation to initiate and maintain healthy behaviors. Importantly, the JOOL Health application has been tested among heterogeneous populations including healthy volunteers and individuals with chronic diseases. These unpublished data demonstrate high user engagement and statistically significant increases in self-reported health behaviors.

We propose a pilot study to estimate the ability of JOOL Health—used alone and also in conjunction with Fitbit devices (i.e., activity tracker and wireless internet-enabled scale)—to increase autonomous motivation to prevent T2DM among individuals with prediabetes who declined participation in a formal DPP (i.e., DPP non-participants). Given that JOOL Health draws on SDT to inspire behavioral change, we hypothesize that autonomous motivation to prevent T2DM will increase to a greater degree among individuals who use JOOL Health compared to individuals who only receive written educational materials about T2DM prevention. Because Fitbit devices can also enhance user motivation by fostering autonomy, competence, and relatedness (through sharing of fitness data) [38]—key SDT tenets of psychological need—we also hypothesize that autonomous motivation to prevent T2DM will increase to a greater degree among individuals who use JOOL Health in conjunction with Fitbit devices compared to individuals who use the JOOL Health application alone. Further, we aim to examine the feasibility of recruiting DPP non-participants and the acceptability (adherence and qualitative experience as reported during semi-structured interviews) of the intervention. We hypothesize that recruiting DPP non-participants may have unique challenges, as these individuals have already declined to participate in one lifestyle intervention. However, as compared to the DPP, this is a low-intensity intervention, which may appeal to individuals seeking a less time-consuming program, and we believe that study participants will find the intervention acceptable. Taken together, these data will inform the design and implementation of a larger trial to test the effect of JOOL Health on clinically relevant outcomes, including weight loss, physical activity, and DPP engagement.

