### Outcome measures

#### Primary outcome measures

The primary outcome will be change in autonomous motivation to prevent T2DM. Autonomous motivation will be measured using the seven-item, validated Treatment Self-Regulation Questionnaire at baseline and 12-week follow-up [42].

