### Sample size

Based on prior studies of autonomous motivation among University of Michigan employees [34], we anticipate that the baseline level of autonomous motivation to prevent T2DM among Premier Care or Grad Care members who decline DPP participation will be 5.7 (measured on a 1 to 7 scale with 1 being the lowest and 7 being the highest). During the 12-week intervention period, we anticipate that autonomous motivation will increase by 0.6 points in the JOOL-only arm and by 0.8 points in the JOOL-plus arm. Assuming a standard deviation of 1.0 for change in autonomous motivation in both arms, 29 participants in each arm will provide 80% power to detect these changes in autonomous motivation in the intervention arms compared to the comparison arm. Prior research demonstrates that a 0.5-point increase in autonomous motivation can lead to greater weight loss and increased physical activity compared to individuals who did not achieve this increase in autonomous motivation [36]. To account for the possibility that some participants may be lost to follow-up during our 12-week intervention, we have conservatively inflated our sample size by 20% to enroll 35 participants in each arm.

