### Data analysis

For all continuous outcomes, we will calculate changes from baseline to 12 weeks. For each continuous outcome, we will then conduct two sample *t* tests to determine whether the mean change for that outcome was statistically significantly different for each intervention arm relative to the comparison arm. For all categorical outcomes, we will use chi-square or Fisher’s exact tests to between-arm changes from baseline to 12 weeks. While we will be conducting multiple tests for statistical significance, we will not adjust our threshold for statistical significance (e.g., using a Bonferroni correction) for multiple comparisons so as to avoid making a type II error in this pilot study. We will conduct all analyses using Stata 14.

Semi-structured interviews will be audio recorded and subsequently transcribed verbatim. Interviews will then be imported into qualitative analysis software. Two investigators will independently read and code transcribed interviews. Interviews will then be coded jointly using consensus conferences. Interviews will be analyzed using directed content analysis [53].

Consistent with a mixed-methods sequential explanatory design [40], we will integrate (i.e., connect) the quantitative and qualitative findings in the final stage of data analysis. In this way, we will interpret our quantitative data in the context of qualitative participant experience.

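### The hypothesis that JOOL-plus raises autonomous motivation more than JOOL-only has no planned analysis, and at the trial's size the contrast can only be an imprecise estimate

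*Protocol article*

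**What the plan says.** The Background of the protocol article states two hypotheses about autonomous motivation. The first is that JOOL Health users will gain more than people given written material only. The second, with its own rationale in Self-Determination Theory, is that motivation will rise to a "greater degree among individuals who use JOOL Health in conjunction with Fitbit devices compared to individuals who use the JOOL Health application alone".

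Under Primary outcome measures: "The primary outcome will be change in autonomous motivation to prevent T2DM". It is a score change from baseline to 12 weeks, so the rule for continuous outcomes in Data analysis governs it. That rule is a two-sample t test for each continuous outcome, to determine "whether the mean change for that outcome was statistically significantly different for each intervention arm relative to the comparison arm".

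The Sample size section expects autonomous motivation to "increase by 0.6 points in the JOOL-only arm and by 0.8 points in the JOOL-plus arm", with this premise on variability: "Assuming a standard deviation of 1.0 for change in autonomous motivation in both arms". It gives 29 per arm for 80% power for the intervention arms against the comparison arm, raised to 35 for loss to follow-up.

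No section gives a test, estimate or interval for JOOL-plus against JOOL-only, and there is no three-group or trend analysis.

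**The concern.** The article does not leave the choice of contrasts open. It names them for every continuous outcome and omits the one that its second hypothesis needs. Hypothesis and analysis therefore disagree within the same document.

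Two things are at stake. First, the third arm differs from the second only by the Fitbit devices, and the plan as written yields no formal statement about that difference. Second, two p-values against one shared comparison arm leave room for an invalid inference: if one JOOL arm reaches significance and the other does not, a reader may take this as evidence about the devices. A difference in significance is not a significant difference, and at this sample size such a split would be common by chance.

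**Working it through.** **Inputs from the Sample size section.** Anticipated increases 0.6 (JOOL-only) and 0.8 (JOOL-plus); SD of change 1.0; 29 per arm, 35 enrolled.

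**Assumptions.** The article states neither the significance level nor its sidedness; I take 0.05 two-sided and also give the one-sided result. It states no change for the comparison arm; I take 0. The 0.2-point device increment does not depend on that second assumption, but the split-significance figures below do.

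**The plan's own figure.** n per arm = 2(z₀.₉₇₅ + z₀.₈₀)² SD²/Δ², with (1.960 + 0.842)² ≈ 7.85.
- Δ = 0.6: 15.70/0.36 = 43.6, so 44 (45 by the t test). Power at 29 is 61% by the t test.
- Δ = 0.8: 15.70/0.64 = 24.5, so 25 (26 by the t test). Power at 29 is 85%.

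The stated 29 is not reproduced from either effect. That is a separate matter, and this point does not rest on it. I use 29 and 35 as given.

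**The missing contrast.** Δ = 0.8 − 0.6 = 0.2.
- Standard error of the difference: √(2/29) = 0.263; √(2/35) = 0.239.
- Power by normal approximation: Φ(0.2/0.263 − 1.960) ≈ 11.5% at 29; Φ(0.2/0.239 − 1.960) ≈ 13.1% at 35. The exact t test gives 11.6% and 13.1%. One-sided at 0.05, the t test gives 18.6% and 20.7%.
- Size for 80% power, two-sided: 15.70/0.04 = 392.5, so 393 per arm (394 by the t test) before dropout. One-sided: 310.
- 95% CI half-width: t₀.₉₇₅,₅₆ × 0.263 = 0.53 at 29; t₀.₉₇₅,₆₈ × 0.239 = 0.48 at 35. Both exceed twice the anticipated 0.2.

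**How often the two planned tests split.** Simulation of 100,000 trials, 29 per arm, one shared comparison arm, SD 1.0, two-sided t tests at 0.05:

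| True effects (JOOL-only, JOOL-plus) | Only JOOL-plus significant | Only JOOL-only significant | Exactly one significant | Direct test significant |
|---|---|---|---|---|
| 0.6, 0.6 | 16.1% | 16.0% | 32.1% | 5.0% |
| 0.7, 0.7 | 12.9% | 13.1% | 26.0% | 5.0% |
| 0.6, 0.8 | 28.4% | 4.5% | 32.8% | 11.8% |

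In the first two rows the devices add nothing. Only the JOOL-plus-alone column would falsely support the stated hypothesis: about 16% at a common effect of 0.6. The 5% for the direct test counts both directions, so the like-for-like comparison is 32% with 5%, or 16% with about 2.5%.

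**The case against.** The case for leaving the plan alone is substantial.

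- **It is a pilot, and the device increment is not a listed aim.** The abstract's aims are to estimate whether JOOL Health can raise motivation and to examine feasibility and acceptability. The JOOL-versus-comparison analyses and the feasibility outcomes are untouched. This stands, and it limits the severity.
- **The contrast can be recovered.** Change is calculated in all arms, and with a shared comparator the device contrast is the difference between the two planned results. A reader might infer that the trial can never address the hypothesis. The documents do not support that: the data will exist, and only the planned analysis omits the contrast. It should still be named in advance.
- **No power is claimed for it.** The Sample size section confines its 80% to comparisons with the comparison arm. The Discussion speaks more loosely of power for between-group differences but does not name this contrast. It would be wrong to say that the article claims power it lacks here.
- **The p-value comparison is not planned.** A reader might infer that the investigators will judge the devices by one arm being significant and the other not. Nothing in the article says so; this is a risk left open by the omission.
- **No choice of intervention hangs on it in the text.** A reader might infer that this result will select JOOL-only or JOOL-plus for the larger trial. The Background and Discussion say only that the findings will inform a larger trial of JOOL Health and give no selection rule. The interviews in both JOOL arms are the documented route to insight into components, though they do not test the hypothesis.

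One further defence fails: the categorical-outcome sentence mentions between-arm comparisons without naming arms, but it cannot cover a continuous primary outcome.

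**Conclusion.** The concern holds as a mismatch inside the article: a hypothesis about the primary outcome is stated, and the specified analysis does not address it. Because the article fixes the contrasts itself, this is not a detail left to a fuller document.

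Adding a test would not make the hypothesis testable at this size. For the implied 0.2 points, power is about 12–13% under an assumed two-sided 5% level, and still only about 19–21% if one-sided. An interval of about ±0.5 points is what the trial can deliver.

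The risk of a misleading split is real in size but inferred in kind. The 16% figure rests on equal true effects of 0.6, no comparison-arm change, 29 analysed per arm and the assumed level. Should-fix: it concerns a secondary contrast in a pilot and does not disturb the main comparisons.

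**What to change.** 1. In Data analysis, prespecify the JOOL-plus minus JOOL-only difference in mean change for the primary outcome, by the same two-sample method as the other contrasts, reported as an estimate with its 95% CI.
2. Label that contrast, and the second hypothesis in the Background, as exploratory, and state that power for a 0.2-point difference is about 12–13%.
3. State that no conclusion about the devices will be drawn from one JOOL arm being significant against comparison and the other not.

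The cost is one extra contrast and a few sentences, with no additional data. The downside is an estimate that is openly imprecise.

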## Methods

This study was approved by the University of Michigan Institutional Review Board. The protocol was designed according to the Standard Protocol Items: Recommendations for Interventional Trials 2013 (SPIRIT). A SPIRIT figure (Fig. 1) and SPIRIT checklist (Additional file 1) are provided. The study is funded by the Blue Cross Blue Shield of Michigan Foundation, and it is registered on ClinicalTrials.gov (NCT03025607).

**Fig. 1 Fig1:**
[figure not shown]
Study flow diagram

### Study design

This study is a 12-week pilot randomized controlled trial. Participants will be randomized to one of three arms: (1) a group that receives information on prediabetes and evidence-based ways to decrease progression to T2DM as well as a list of resources for mHealth tools for monitoring diet, physical activity, and weight (comparison); (2) a group that receives the same information as group 1 and also the JOOL Health mobile phone application (JOOL-only); and (3) a group that receives the same information as group 1 and also the JOOL Health mobile phone application and Fitbit devices (i.e., activity tracker and wireless internet-enabled scale) whose results can be uploaded to JOOL Health (JOOL-plus). We will use a mixed methods approach with a sequential explanatory design, which is to say that quantitative data and qualitative data will be collected in two consecutive phases within the study [39]. Specifically, in the first phase, we will collect and analyze the quantitative data (e.g., surveys and weight). In the second phase, we will collect and analyze qualitative, semi-structured interview data from a purposive sample of 20 participants with differing levels of engagement and success with the intervention. The rationale for this approach is that the qualitative data will help to clarify these findings by exploring participants’ experiences and perspectives in more depth [40]. Additionally, through qualitative interviews, we will explore the acceptability of the JOOL Health application among JOOL-only participants and the acceptability of the JOOL Health application and Fitbit devices among the JOOL-plus participants.

### Study setting

The intervention will be delivered remotely. Individuals in each arm of the study will receive study materials by postal mail and/or e-mail. A study team member will be available by telephone to help participants troubleshoot technical issues that may arise with the study devices and to address study-related questions or concerns.

### Study participants

Inclusion criteria are (1) non-participation in a formal DPP at least 6 months after invitation to participate by the University’s self-funded insurers, Premier Care or Grad Care; (2) prediabetes based on the American Diabetes Association criteria of hemoglobin A1c (HbA1c) 5.7 to 6.4%; (3) access to a personal smartphone; and (4) access to home wireless internet. We will exclude women who are pregnant or intend to become pregnant during the intervention period. All eligible study participants are employees, retirees, and students of this university or their dependents.

### Recruitment

A member of the study team will contact by telephone a random subset of Premier Care and Grad Care DPP non-participants. Individuals interested in study participation will then be screened to ensure they meet study eligibility criteria, and informed consent will be obtained electronically using the RedCap survey platform [41].

### Allocation

Individuals who meet study inclusion criteria and consent to study participation will be randomized using a web-based tool, the University of Michigan computerized randomization system (TATUM—Treatment Assignment Tool-UM), which allows for blinded treatment allocation. We will use stratified randomization with variable block lengths to ensure a balance of age and gender between groups. Recruitment and randomization will be ongoing until we have 35 individuals in each arm of the study.

### Intervention

All participants (*N* = 105) will receive information regarding prediabetes, evidence-based T2DM prevention strategies, and mHealth resources to help monitor food intake and composition, weight, and physical activity (e.g., MyFitnessPal). All participants will be encouraged to engage in self-monitoring and will be provided information on the benefits of daily weighing and monitoring of food and physical activity.

Participants in the JOOL-only and JOOL-plus arms will receive instruction by e-mail on how to use their respective mHealth applications. Participants in both intervention arms will be asked to use JOOL Health on a daily basis. JOOL Health will deliver tailored messages to individuals based on the daily information they enter in the following behavioral health domains: sleep, presence, activity, creativity, and eating. Additionally, the tailored messaging will be informed by contextual factors (e.g., local weather and day of the week). Participants in the JOOL-plus arm will also be asked to perform daily weights using a Fitbit wireless internet-enabled scale and to wear a Fitbit physical activity tracker. These devices will interface with the JOOL Health platform, and the data will inform JOOL-delivered tailored messages.

